# Simplifying and optimising management of acute malnutrition in children aged 6 to 59 months: study protocol for a 3 arms community-based individually randomised controlled trial in decentralised Niger

**DOI:** 10.1186/s13063-021-05955-6

**Published:** 2022-01-28

## Abstract

**Background:**

Simplified approaches of acute malnutrition (AM) treatment have been conducted over the past 5 years intending to unify processes and increase coverage among children aged 6 to 59 months without medical complication. The Optimsing treatment for Acute Malnutrition (OptiMA) and the Combined Protocol for Acute Malnutrition Study (ComPAS) are mid-upper arm circumference (MUAC)-based approaches treating children with MUAC < 125 mm or oedema with one sole product—ready-to-use therapeutic food—at a gradually tapered doses. This trial aims to compare the OptiMA and ComPAS strategies to the standard nutritional protocol of Niger assessed by a favourable outcome in the treatment of uncomplicated AM at 6 months post-randomisation and in terms of recovery rate after treatment of uncomplicated SAM (WHZ < − 3 or MUAC < 115mm or oedema) and among the most vulnerable children (MUAC < 115mm or oedema).

**Methods:**

A non-inferiority individually randomised controlled clinical trial was conducted at the primary health centres level and in the community in the Zinder region in Niger in March 2021. Participants are children aged 6–59 months attending outpatient health centres with MUAC < 125mm or oedema without medical complications. All participants are followed for 6 months. Simplified strategies propose a gradual reduction of RUTF according to MUAC and weight in OptiMA and MUAC only in ComPAS. Favourable outcome is compositely defined at 6 months post-inclusion as being alive, not acutely malnourished by the definition applied at inclusion and without any additional episode of AM throughout the 6-month observation period. Recovery is defined throughout the 6 months post-randomisation by a minimum of 4-week duration of treatment, an axillary temperature < 37.5°C, an absence of bipedal oedema and a MUAC ≥ 125 mm for two consecutive weeks. The sample size calculation required 567 children per arm for the main objective, 295 and 384 children per arm for the secondary objectives among SAM and MUAC < 115 mm children, respectively. Per-protocol and intention-to-treat analyses will be conducted for each outcome.

**Discussion:**

This trial is intending to generate much-needed evidence on various simplified and optimised AM treatment approaches and to participate in reaching a consensus on such nutrition protocols.

**Trial registration:**

ClinicalTrials.govNCT04698070. Registered on January 6, 2021

**Supplementary Information:**

The online version contains supplementary material available at 10.1186/s13063-021-05955-6.

## Introduction

Acute malnutrition (AM) affected an estimated 45.5 million children under 5 years of age in 2020, including 13.6 million suffering from severe acute malnutrition (SAM) [1], and was an underlying cause of 800,000 yearly deaths worldwide [2]. The coverage rate for community-based management of acute malnutrition (CMAM) programmes is low, with less than 25% of all children suffering from SAM being admitted to treatment, and an even lower proportion of children with moderate acute malnutrition (MAM) accessing support [3]. This low coverage is multi-factorial with the following two issues having been particularly underlined: first, the complexity of nutrition programming which uses different case definitions based on weight-for-height *Z*-score (WHZ) and/or middle-upper arm circumference (MUAC) and/or oedema; second, the quantity of ready-to-use therapeutic food (RUTF) given to children in current standard protocols are not optimum [4], which negatively impacts the actual cost of such programmes. In standard protocols, RUTF quantity prescribed in the first weeks of treatment is paradoxically often less important than what is given to children reaching recovery (MUAC > 125 and/or WHZ > − 2), because the weekly ration is determined by the child’s weight, which increases as the child recovers. There is a growing body of evidence suggesting that weight gain is highest in the first month of treatment and then plateaus [5]. There would therefore be no benefit of increased RUTF ration during the course of treatment, and progressive reduction of RUTF quantity seems to be a more rational use of this treatment.

In addition, SAM and MAM programmes are chronically underfunded with less than 40% of SAM cases treated globally in 2019 and as few as 16% of MAM cases reached by the World Food Program in 2017 [6, 7]. These two programmes are managed separately, with programmes overseen by different UN agencies, and using different protocols and products. An optimised allocation of resources is therefore urgently needed. To address these issues, simplified and optimised approaches have been conducted in Sub-Saharan Africa over the past 5 years intending to simplify processes and increase coverage among children aged 6 to 59 months without medical complications [8]. Protocol modifications are varied and still evolving, but a common approach using 1- only MUAC or oedema for admission, follow-up, and discharge, 2- a simplified definition of AM by MUAC < 125 mm or presence of bipedal oedema, and 3- a single product for treatment (RUTF) at different gradually reduced dosages has been evaluated in recent randomised controlled trials.

The first cluster-randomised controlled trial based on MUAC < 125mm or oedema was exploring the efficacy of an integrated MUAC-based SAM/MAM treatment protocol using RUTF only but at different doses for children < 115mm (175 kcal/kg/day) and 115 to 124 mm (75 kg/kcal/day) compared to the standard protocol in Sierra Leone in 2013 [9]. The results showed that the integrated programme had a reduced caseload of SAM, due to earlier treatment of children presenting as MAM, with a similar recovery rate (83–95% CI 81–85 vs. 79–95% CI 77–82) and higher coverage (71% vs. 55%, *p* = 0.0005).

The Optimsing treatment for Acute Malnutrition (OptiMA) strategy has been developed in a research consortium between humanitarians from the Alliance for International Medical Action (ALIMA) non-governmental organisation and scientists from the French National Institute for Health and Medical Research (Inserm). The OptiMA RUTF ration is calibrated to the child’s degree of wasting based on the combination of MUAC status and weight. Thus, more nutritional feeding is given to the most severely malnourished and then gradually reduced as the child’s MUAC increased. Children with MUAC < 115 mm or oedema receive 175 kcal/kg/day of RUTF. Children with MUAC 115–119 mm, either at admission or during the course of treatment, receive 125 kcal/kg/day of RUTF, and children with MUAC ≥ 120 mm receive 75 kcal/kg/day of RUTF (with a minimum of one sachet/day) until discharge from the programme. The OptiMA strategy was first implemented in a proof-of-concept single-arm trial in Burkina Faso in 2018 [10]. The results showed a recovery rate that exceeded SPHERE standards among children admitted with MUAC < 125mm (86.3%; 95% CI 85.4–87.2%) with an excellent health worker adherence to the new RUTF table. However, recovery among children admitted with a MUAC < 115 mm or oedema was poorer than anticipated (70.4%; 95% CI 67.5–73.5%). Then, an individually randomised non-inferiority controlled trial compared the OptiMA strategy to the national protocol was implemented in the Democratic Republic of the Congo (DRC) in 2019 [11]. The OptiMA protocol treated 29% more children with 20% less nutritional inputs compared to the standard protocol. A pilot non-comparative cohort study on 1111 acutely malnourished children per the OptiMA definition was implemented in 2019 in Niger and showed a similar result to the one observed in the above-mentioned study in Burkina Faso with a global recovery rate among children admitted with a MUAC < 125 mm that exceeded 80% ( [10] and Personal communication, 2020). However, recovery among the 290 children admitted with a MUAC < 115 mm remained low (57.7%), partly explained by a high proportion of children (34.1%) not reaching the exit criteria after 10 weeks of participation in the programme (Personal communication, 2020).

The Combined Protocol for Acute malnutrition Study (ComPAS) was developed by the International Rescue Committee (IRC) and consists in reducing the dosage according to the child’s MUAC during the outpatient follow-up and has the simplest dosing regimen ever tested: 2 RUTF sachets/day to children with MUAC < 115 mm or oedema and 1 RUTF sachet/day for children in the 115–124 mm MUAC category [12]. The main advantage of this strategy is that it can be implemented by community health workers, regardless of literacy level and without other anthropometric tools rather than a MUAC tape. Simplification and decentralisation of nutrition programming to the community level stand the best chance of increasing service coverage. A cluster-randomised controlled non-inferiority trial was implemented in Kenya and South Sudan in 2017 and showed that recovery in the ComPAS arm (76.3%) was non-inferior to that of the standard care arm (73.5%): risk difference of 0.03, 95% CI − 0.05 to 0.10, *p =* 0.52 [13]. The average amount of RUTF for SAM children was significantly lower under the ComPAS protocol (122 sachets) compared to the standard one (193 sachets) [13].

These simplified nutrition protocols deviate from existing normative guidance, and despite the MUAC-based common approach, there is currently a lack of consensus on these modifications. More evidence is needed prior to developing such simplified and optimised approaches at scale. Burning issues include which dosage is better to implement and what is the impact of such reduced regimens on recovery, especially among the most vulnerable children (MUAC < 115 mm).

This is exactly what this community-based non-inferiority trial proposes by comparing the OptiMA and ComPAS strategies to the current Niger protocol of AM treatment. We hypothesised that the OptiMA and ComPAS strategies would be as effective as the current Niger national protocol currently in use in children aged 6 to 59 months. This hypothesis will be assessed by reaching a favourable outcome in the treatment of uncomplicated SAM and MAM at 6 months post-randomisation and in terms of recovery rate in the treatment of uncomplicated SAM (WHZ < − 3 or MUAC < 115 mm or oedema) and also among children admitted with MUAC < 115 mm.

## Objectives

The principal objective aims to determine, 6 months after inclusion, whether the OptiMA strategy or ComPAS strategy leads to a favourable outcome which is non-inferior to what Niger standard protocol, in use in the same outpatient health facilities, provides. The definition of a favourable outcome is described in the “Study outcomes” section.

Two main secondary objectives for this trial are as follows. The first one is to determine whether the recovery rate of children with uncomplicated SAM according to the current WHO definition [14] (e.g. MUAC < 115 mm or WHZ < − 3 or bilateral oedema) managed under the simplified OptiMA or ComPAS strategies is non-inferior to that of the national standard protocol of Niger. The second one is to determine whether the recovery rate of children admitted with MUAC < 115 mm or oedema (+, ++) managed under the simplified OptiMA or ComPAS strategies is non-inferior to that of the national standard protocol of Niger.

Other secondary objectives include description and comparison between the three study arms of the following outcomes: cost-effectiveness analysis, RUTF consumption, relapse after nutritional recovery, non-response after outpatient follow-up, recovery, and success in children who present with both wasting and stunting at inclusion, and to describe the nutritional and clinical status of children hospitalised while enrolled in the study.

## Methods

This protocol follows the Standard Protocol Items: Recommendations for Interventional Trials (SPIRIT) guidelines see Additional file 1 [15].

### Trial design and study period

This study is a non-inferiority individually randomised controlled clinical trial conducted at the health centre level and in the community. Participants are randomly assigned to either the OptiMA or ComPAS strategy arms (intervention = OptiMA or ComPAS) or the national standard protocol arm (control = standard). Inclusions started on March 23, 2021, for a 9-month period with an expected end in December 2021. All participants are followed for a 6-month period post-randomisation, with an active phase expected to end in June 2022.

### Study setting

The trial took place in Mirriah district, Zinder region, in the south-east of Niger and was nested within a medical and nutritional emergency humanitarian project under ALIMA supervision since 2009. The Mirriah district is one of the most populated in Niger, with an estimated population of 700,000 in 2019 and approximately 20% of children aged under 5 years old. Zinder region is particularly affected by AM, with prevalences of SAM and MAM showing sharp increases in 2020 at rates estimated to be as high as 4.9% (95% CI 4.2–5.8) and 13.0% (95% CI 11.7–14.5), respectively [16].

During the trial preparation phase, we visited all health centres in the district to select four of these according to the following criteria: outpatient therapeutic programme (OTP) activities, population size covered, and logistic conditions. These four health centres cover 242 villages with an estimated population of 178,535. Overall, 82 (34%) villages are more than 10 km away from the health centre.

### Eligibility criteria

Children aged 6–59 months, living for more than 6 months in one of the four health areas, and meeting at least one of the three following AM criteria are eligible for inclusion in the trial: MUAC < 125 mm and/or bilateral pitting oedema (+/++) and/or WHZ < − 3. Children with a medical complication requiring hospitalisation; no appetite; oedema grade +++; with a known allergy to milk, peanuts, or RUTFs; with a chronic disease (such as sickle cell anaemia, trisomy 21, congenital heart disease, neurological disease); or children already enrolled in a malnutrition programme are excluded from the trial.

Two categories of children are included in the trial but not eligible for randomisation for ethical concerns. First, children with WHZ < − 3 and MUAC ≥ 125 mm without oedema are systematically included in the control arm, as they are not eligible for RUTF regarding the definition of wasting in neither OptiMA nor ComPAS strategies. Second, children with a sibling already enrolled in the trial are systematically allocated to the study arm of the index sibling. Ultimately, children with MUAC < 125 mm and/or bilateral oedema and with no sibling already included in the trial are individually randomised.

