### Study outcomes

The primary outcome will be judged by a binary composite indicator. Children classified as “favourable outcome” fulfil all of the following criteria: alive, not acutely malnourished per the anthropometric definition applied at inclusion (MUAC > 125mm and WHZ > − 3, and no oedema) and not having an additional episode of AM throughout the 6-month observation period. This outcome is measured at 6 months after randomisation. All other children are classified as “unfavourable outcome”.

The main secondary outcome #1 will be determined among children who meet the current WHO definition of SAM at inclusion (MUAC < 115 mm or WHZ < − 3 or oedema +, ++). The main secondary outcome #2 will be determined among children admitted with a MUAC < 115mm or oedema (+, ++). For these two subgroups, recovery is defined in each arm by a 4-week minimum duration of treatment, an axillary temperature < 37.5 °C, and an absence of bipedal oedema and a MUAC ≥ 125 mm for two consecutive weeks. This outcome is measured throughout the 6 months post-randomisation, meaning a child will be considered as recovered if he reaches these criteria during the 6-month follow-up in outpatient or village visits. Additional secondary outcomes are listed in Table 1.

**Table 1 Tab1:** Primary and secondary outcomes in the OptiMA Niger trial

	Measurement variable	Method of aggregation	Time point

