**Main secondary**			
Recovery	Composite: absence of bipedal oedema and a MUAC > 125 mm for two consecutive weeks, a 4-week minimum duration of RUTF treatment, and a good clinical health (without fever)	Proportion	Throughout the 6-month follow-up period
**Secondary**^a^			
Cost-effectiveness	Incremental cost-effectiveness ratio (ICER)	Ratio	Throughout the 6-month follow-up period
Consumption of RUTF per children with a favourable outcome	Sachets of RUTF consumed	Mean	6-month post-inclusion
Consumption of RUTF per recovered children	Sachets of RUTF consumed	Mean	End of RUTF treatment initiated at inclusion
Average daily weight gain in SAM children recovered	g/kg/day	Daily	End of RUTF treatment initiated at inclusion
Average daily MUAC gain in SAM children recovered	mm/day	Daily	End of RUTF treatment initiated at inclusion
Hospitalisation	Children with at least one episode of hospitalisation	Proportion	Throughout the 6-month follow-up period
Relapse to a new episode	Children with MUAC < 125 or WHZ < − 3 *Z*-score or oedema after RUTF treatment	Proportion	After recovering from the first episode of acute malnutrition
Non-response	Children who did not reach the recovery criteria	Proportion	16 weeks after inclusion
WaST	Children associated with severe and moderate stunting with acute malnutrition	Proportion	Throughout the 6-month follow-up period

^a^All the secondary outcomes will be analysed for the overall population (MUAC < 125 mm or WHZ < − 3 or oedema) and for the secondary populations (SAM WHO and MUAC < 115 mm or oedema)

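### Control-only, non-randomised children (WHZ < −3 with MUAC ≥ 125 mm) fall inside the stated populations for main secondary outcome #1 and the overall comparisons

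*Protocol article*

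**What the plan says.** Eligibility criteria: "Two categories of children are included in the trial but not eligible for randomisation for ethical concerns". The first category is children with WHZ < −3, MUAC ≥ 125 mm and no oedema, who "without oedema are systematically included in the control arm, as they are not eligible for RUTF" under OptiMA or ComPAS. The second is siblings: "children with a sibling already enrolled in the trial are systematically allocated to the study arm of the index sibling". Only children with MUAC < 125 mm and/or oedema and "with no sibling already included in the trial are individually randomised".

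Study outcomes: "The main secondary outcome #1 will be determined among children who meet the current WHO definition of SAM at inclusion", spelled out as MUAC < 115 mm or WHZ < −3 or oedema. By contrast, "The main secondary outcome #2 will be determined among children admitted with a MUAC < 115mm or oedema". Recovery for both requires at least 4 weeks of treatment, no fever, no oedema and MUAC ≥ 125 mm for two consecutive weeks; WHZ plays no part. The primary favourable outcome does include WHZ: the child must be above −3 at 6 months.

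Table 1, footnote a: "All the secondary outcomes will be analysed for the overall population", defined as MUAC < 125 mm or WHZ < −3 or oedema. The primary outcome has no population definition of its own.

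Statistical analysis: both intention-to-treat and per-protocol comparisons between randomisation arms are planned. Neither set is described as omitting the non-randomised children.

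**The concern.** A non-inferiority comparison depends on the control rate coming from the same kind of children as the experimental rates. Here one type of child can occur only in the control arm, by rule, and the written population definitions bring that type into the comparison. The difference between arms then mixes the effect of the strategy with a difference in case mix that randomisation did not create and cannot balance.

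For main secondary outcome #1, which the protocol powers separately, the likely effect is a control rate that is too high and a real chance of missing non-inferiority. If the control rate moved down instead, which is possible for the primary outcome, the risk would be a false claim of non-inferiority.

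**Working it through.** **1. Do the definitions admit the control-only group?** Take a child with WHZ < −3, MUAC ≥ 125 mm and no oedema.

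- Main secondary #1 (MUAC < 115 mm or WHZ < −3 or oedema): admitted through WHZ.
- Overall population (MUAC < 125 mm or WHZ < −3 or oedema): admitted through WHZ. Children with MUAC < 125 mm or oedema are already in, so the WHZ term adds only the control-only children.
- Main secondary #2 (MUAC < 115 mm or oedema): not admitted.
- Primary: such a child is in the trial and followed for 6 months, and no text removes the child.

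**2. The plan's own sample sizes.** Inputs (Sample size; Statistical analysis): margin 0.10; one-sided alpha 1.25% (z = 2.2414); power 90% (z = 1.2816) or 80% (z = 0.8416); equal rates of 68%, 82% and 74%; 5% inflation.

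n = (z_alpha + z_power)² × 2p(1 − p) / 0.10², then divided by 0.95:

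- Primary, p = 0.68: 540.1, inflated 568.6 (stated 568).
- Main secondary #1, p = 0.82: 280.6, inflated 295.4 (stated 295).
- Main secondary #2, p = 0.74: 365.8, inflated 385.0 (stated 384).

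The stated sizes reproduce to within about one child, and they assume the same rate in every arm.

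**3. Effect on main secondary #1.** Let k be the control-only share of the control SAM set and q its recovery rate. Neither is in the document; both are assumptions.

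- Control rate: pc = 0.82(1 − k) + qk, so the shift is k(q − 0.82).
- Power = Φ[(0.10 − shift)/SE − 2.2414], with SE = √[pc(1 − pc)/n0 + 0.82 × 0.18/281].
- n0 = 281/(1 − k), meaning the control-only children come on top of 281 evaluable randomised controls.

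With k = 0, SE = 0.0324 and power is 80.1%.

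| k | q | control rate | shift (points) | power |
|---|---|---|---|---|
| 10% | 90% | 82.8% | +0.8 | 76% |
| 10% | 95% | 83.3% | +1.3 | 71% |
| 10% | 99% | 83.7% | +1.7 | 67% |
| 20% | 90% | 83.6% | +1.6 | 70% |
| 20% | 95% | 84.6% | +2.6 | 59% |
| 20% | 99% | 85.4% | +3.4 | 49% |

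If these children instead count within the 281 (n0 = 281), power at q = 95% is 68.5% for k = 10% and 54.4% for k = 20%.

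**4. Effect on the primary.** Same formula, p = 0.68, 540 evaluable per arm, control-only children counted within the 540. Let r be their success rate (assumed). Type I error is evaluated with the experimental arm at 0.58, exactly at the margin relative to randomised controls.

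- k = 10%, r = 50%: control 66.2%, shift −1.8 points; (0.10 − 0.082)/0.0294 − 2.2414 = −1.63, so type I error is 5.2% instead of 1.25%.
- k = 20%, r = 50%: shift −3.6 points, type I error 15.3%.
- k = 10%, r = 80%: shift +1.2 points, power 80.9% instead of 90%.

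The same mechanism can push either way, and nothing in the document says which.

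**The case against.** The best case for the plan is that it means a randomised comparison. The Statistical analysis section refers to randomisation arms and intention-to-treat. The Randomisation section describes the WHO-SAM group as drawn from randomised strata and says that recruitment and randomisation of SAM children continue until the secondary sample sizes are met. The abstract describes participants by MUAC and oedema only. A separate analysis plan, not shown here, may define the sets. These are fair pointers, and they mean one cannot say the sponsor will analyse the data this way. They do not override two explicit population definitions that admit WHZ < −3 without a MUAC limit. The second randomisation stratum, as printed, has no upper MUAC limit either.

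Four stronger readings are tempting and not supported:

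- *All overall-population outcomes are biased against the simplified strategies.* Favourable outcome requires WHZ > −3, which these children fail at entry, and relapse counts WHZ < −3. Control could look worse, not better.
- *These children recover almost automatically.* They still need 4 weeks of treatment, no fever, no oedema and a sustained MUAC. Default, death or MUAC loss can prevent recovery.
- *Every main comparison is affected.* Main secondary #2 cannot contain this group.
- *Siblings add to the control-only imbalance.* They follow the index child's randomised arm, so they occur in all three arms. What remains is an allocation known before enrolment and within-family correlation. The document gives no figure for either, and selective presentation by caretakers is conjecture.

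**Conclusion.** Wrong as written. The eligibility rule and the population definitions together put a non-randomised, control-only group into main secondary #1 and the overall comparisons.

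For main secondary #1, inflation of the control rate is probable, because recovery ignores WHZ and these children enter above the MUAC threshold. The figures of 0.8–3.4 points and 76–49% power are illustrative: they rest on an assumed 10–20% share, an assumed 90–99% recovery rate and a true rate of 82% among randomised children in all arms. For the primary and other overall outcomes, neither direction nor size can be settled from the document. The sibling rule is a minor point.

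**What to change.** In the Statistical analysis section, the Study outcomes section and Table 1, footnote a:

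- Limit all intention-to-treat and per-protocol between-arm comparisons to children who meet the anthropometric criteria for randomisation, MUAC < 125 mm and/or oedema.
- Restate the main secondary #1 population as MUAC < 115 mm or oedema, or MUAC 115–124 mm with WHZ < −3. Main secondary #2 needs no change on this account.
- Report the WHZ < −3, MUAC ≥ 125 mm children descriptively, as a separate group.
- State that these children do not count towards 568 or 295 per arm.
- For siblings, use household-clustered standard errors, or show each result with and without them. Either is defensible.

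This is a wording change before analysis and needs no new data. If the control-only children have not been counted towards the targets, the stated sizes stand. If they have, restricting the comparison costs some power. With 95% of the stated numbers evaluable (540 and 280 per arm), an assumed 10% or 20% share removed from the control arm gives 88.2% or 86.0% for the primary (from 90.0%), and 77.6% or 74.7% for main secondary #1 (from 79.9%).
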